## Abstract

**Background:**

The aim of the current study is to evaluate the efficacy of an exercise intervention to reduce work-related fatigue. Exercise is a potentially effective intervention strategy to reduce work-related fatigue, since it may enhance employees’ ability to cope with work stress and it helps to detach from work. However, based on available research, no clear causal inferences regarding its efficacy can be made. This RCT therefore investigates whether exercise is effective in reducing work-related fatigue, and in improving other indicators of employees’ mental and physical well-being and performance.

**Methods/design:**

A two-arm parallel trial will be conducted. Participants (*N* = 108) who experience high levels of work-related fatigue will be randomized at a 1:1 ratio to a 6-week exercise intervention or wait list (control). The exercise intervention consists of three one-hour low-intensity outdoor running sessions a week. Each week, two sessions take place in a group under supervision of a trainer, and one session is completed individually. The running sessions will be carried out during leisure time. The primary outcome is work-related fatigue. Secondary outcomes include work ability, self-efficacy, sleep quality, cognitive functioning, and aerobic fitness. These data will be collected at pre-intervention, post-intervention, and at 6 weeks and 12 weeks after the intervention. In addition, weekly measures of employees’ well-being, and exercise activities (i.e. type, frequency, and duration) and experiences (i.e. pleasure, effort, and detachment) will be collected during the intervention period.

**Discussion:**

This study will compare an exercise intervention to a wait list. This enables us to examine the effect of exercise on work-related fatigue compared to the natural course of these symptoms. As such, this study contributes to a better understanding of the causal link between exercise and work-related fatigue. If the intervention is proven effective, the results could provide a basis for future ‘effectiveness’ trials in which the (implementation of the) intervention can be investigated among a broader defined population in a less standardized way, eventually leading to better evidence-based policies and practices to employees, employers, health practitioners, and policy makers concerning the effect of exercise on work-related fatigue.

**Trial registration:**

NTR5034. Registered 10 March 2015.

## Background

Work-related fatigue is a global concern (estimated at 22 % among employees in Europe [1]) and is thought to at least partly result from prolonged stress at the work place [2]. Employees who experience work-related fatigue often have poorer work performance [3], are more frequently absent from work [4], and are at higher risk for ill health, such as cardiovascular diseases [5]. If work-related fatigue becomes more severe, it can result in (long-term) clinical burnout [2]. Given the prevalence of work-related fatigue, and the negative impact on employees’ work and health, it is valuable to examine potential intervention strategies to reduce these symptoms.

Regular exercise may be an eligible intervention strategy to reduce work-related fatigue. Assets of exercise include its accessibility, low costs [6], and positive side effects, such as reduced risk for cardiovascular diseases [7].

### Exercise and work-related fatigue

The potential beneficial effects of exercise on work-related fatigue can be understood from a combination of various (interconnected) physiological and psychological mechanisms. For instance, it has been proposed that exercise enhances employees’ ability to (physically and psychologically) cope with work stress [8, 9]. Others found that exercise helps to detach from work [10], and enhances positive affect [11] facilitating employees in replenishing their energy levels. In addition, research indicates that exercise impacts certain neural circuits and the release and uptake of chemicals in the brain, which are associated with better mental health [12, 13].

Despite these proposed theoretical notions, based on available empirical evidence no clear causal inferences can be made about the effect of exercise on work-related fatigue. This is because knowledge about this relation is largely based on correlational studies [14–18], and the relatively few available intervention studies suffered from one or more methodological shortcomings [19–22]. In well-designed intervention studies, exercise was conducted among students [23] (which leaves the question open whether results can be generalized to employees), or exercise was combined with other intervention ingredients [24] (which makes it impossible to know to what extent the beneficial effects were due to exercise). Furthermore, research suggests that it may be more difficult for employees with high levels of work-related fatigue to engage in regular exercise [16–18]. Taken together, there is a need for methodologically sound intervention studies to better understand the causal link between exercise and work-related fatigue.

Against this background, the aim of the current study is to test the effect of exercise on work-related fatigue with a design that allows for strong causal inferences. To this end, employees with high levels of work-related fatigue who currently do not engage in regular exercise will be randomly assigned to either a six-week exercise intervention or a wait list (control group). This enables us to test the effect of exercise on work-related fatigue compared to the ’natural course’ of these symptoms. In the intervention, we will use running as a form of exercise, because it is easy to implement: only running shoes are needed and it is high in flexibility in terms of time and place. Based on the proposed psychological and physiological working mechanisms and available empirical research, we hypothesize:*Hypothesis 1*: the exercise intervention is effective in reducing work-related fatigue

Additionally, we will measure the impact of exercise on five secondary outcomes, which are relevant for employees with high levels of work-related fatigue, and which may be expected to be positively affected by means of regular exercise.

### Exercise and self-efficacy

First of all, we will study the effect of exercise on work-related and general self-efficacy. It has been found that employees with high levels of work-related fatigue often experience reduced self-efficacy in their functioning at work [3]. On the other hand, it has been proposed that exercise is accompanied by a sense of mastery, which can increase self-efficacy with respect to exercise [25], and other life domains [26]. Since this current research is carried out in a work context, we will investigate whether exercise benefits work-related self-efficacy. We hypothesize:*Hypothesis 2a:* the exercise intervention is effective in improving work-related self-efficacy among employees with high levels of work-related fatigue

As the sense of mastery gained by exercise may also be translated in a general confidence in succeeding at tasks and in situations (i.e. general self-efficacy), we expect:*Hypothesis 2b*: the exercise intervention is effective in improving general self-efficacy among employees with high levels of work-related fatigue

### Exercise and sleep

Second, we will study the impact of exercise on employees’ sleep quality, and sleep duration. Sleep quality refers to ‘how well someone sleeps’, and is, for instance, characterized by the number of awakenings during the night and the degree of tiredness upon waking [27]. It has been found that work-related fatigue is negatively related to sleep quality [28]. Concurrently, previous studies have reported that regular exercise improves sleep quality [29]. In accordance with these empirical findings, we expect:*Hypothesis 2c:* the exercise intervention is effective in improving sleep quality among employees with high levels of work-related fatigue

Research suggests that exercise may also impact employees’ sleep duration [29]. Various pathways have been proposed to explain this relationship, such as cytokine concentration changes (for a review; see [30]). In agreement with these proposed mechanisms and empirical evidence, we expect:*Hypothesis 2d*: the exercise intervention is effective in improving sleep duration among employees with high levels of work-related fatigue

### Exercise and work ability

Third, we will investigate whether exercise benefits work ability. Work ability concerns the physical, psychological, and social capability of an employee to effectively cope with work demands [31]. It has been found that a high level of work-related fatigue is a risk factor for decreased work ability [32]. As exercise contributes to psychological [11], social [33], and physical health [34], it can be expected that exercise enhances employees’ capacity to cope with work demands. Indeed, the scarce available empirical research shows that regular exercise is positively related to work ability [35]. Therefore, we expect:*Hypothesis 2e:* the exercise intervention is effective in improving work ability among employees with high levels of work-related fatigue

### Exercise and cognitive functioning

Fourth, the effect of exercise on cognitive functioning will be studied. Research shows that employees with high levels of work-related fatigue often display cognitive deficits, such as impaired executive functioning and cognitive problems in daily life [36, 37]. Executive functioning refers to a set of cognitive brain processes involving mental control and self-regulation [38]. Evidence from a broad range of studies shows that exercise is linked to beneficial changes in cognitive functioning, in particular executive functions [39, 40]. Therefore, we hypothesize:*Hypothesis 2f:* the exercise intervention is effective in improving cognitive functioning among employees with high levels of work-related fatigue

### Exercise and aerobic fitness

Fifth, we will examine the effect of exercise on aerobic fitness. Aerobic fitness may be defined as the ability to deliver oxygen to the muscles and to utilize it to generate energy during exercise [41]. Employees with high levels of work-related fatigue are found to have relatively low fitness levels [42]. On contrary, the evidence regarding the positive effects of exercise on fitness is overwhelming [43], but effects also depend on the type, frequency, intensity, and duration of exercise [44]. Because participants in our study will change from not exercising to regular (i.e. 3 times a week) exercising, we hypothesize:*Hypothesis 2 g:* the exercise intervention is effective in improving aerobic fitness among employees with high levels of work-related fatigue

For all primary and secondary outcomes (except cognitive functioning, due to possible learning effects), we will include follow-up measures to examine whether the proposed beneficial effects of exercise last over time.

### Weekly trajectories of employee well-being

Next to measuring the effect of exercise on these primary and secondary outcomes after the intervention period, it is also valuable to examine employees’ well-being trajectories during the intervention period. This prevents the intervention period of being a ‘black box’, in which it remains unknown which changes take place at what time. Therefore, in the current study, we will pay close attention to employee well-being during the intervention period. We will employ weekly self-administered single-item measures of fatigue, self-efficacy and sleep, which correspond to our primary and secondary outcomes. Additionally, we will investigate other single-item indicators of employee well-being, such as mood, to capture a broader range of the effects of the intervention. By doing so, we aim to provide a more fine-grained insight in how these different indicators of employee well-being develop during the intervention period, and whether weekly trajectories of these indicators differ between conditions. Although it is not possible to predict at what time these indicators change as a result from the intervention, we generally expect that:*Hypothesis 3*: during the course of the intervention period, participants in the exercise condition show a larger improvement in weekly well-being compared to participants in the control condition.

### Compliance, and subjective exercise experiences as moderators of employee well-being

Finally, we will investigate possible moderators in the relation between exercise and employee well-being: compliance to the intervention and subjective exercise experiences. This could give us information for whom or under what conditions the intervention works best. Concerning compliance, we will measure participants’ compliance with the running sessions of the exercise intervention. Participants who attend more of the running sessions of the intervention will likely also benefit more from the beneficial changes brought about by exercise. Therefore, we expect:*Hypothesis 4a*: during the course of the intervention period participants with higher attendance rates show larger improvement in weekly well-being compared to participants with lower attendance rates

It has been argued that not only the type of activity (i.e. exercise) matters for beneficial effects on employee well-being, but that also the subjective experience of the activity is important [45, 46]. Therefore, we will pay attention to three ratings of employees’ experiences (i.e. ‘pleasure’, ‘detachment’, and ‘effort’) during the running sessions, and examine how these experiences may or may not moderate exercise intervention efficacy. As research has shown that effects of activities, such as exercise, on well-being are stronger when these activities are enjoyed [46, 47], we expect in this current study:*Hypothesis 4b:* participants who rate their weekly running sessions as pleasant show a larger improvement in weekly well-being than participants who rate these sessions as less pleasant

Furthermore, as it has been found that employees who during activities experience psychological detachment from work (i.e. mentally distancing oneself from work), show better well-being outcomes [45], we hypothesize:*Hypothesis 4c:* participants who psychologically detach from work during their weekly running sessions show a larger improvement in weekly well-being than participants who cannot psychologically detach from work during these sessions

For the experience of effort, it is difficult to formulate a hypothesis. Although exercise is an effortful activity in nature, research suggest that a too high intensity of exercise could lead to unbeneficial outcomes in well-being [48]. We will therefore investigate the experience of effort in relation to the weekly well-being outcomes in a more exploratory way.

## Methods/design

### Study design

The study design will be a two-arm parallel randomized controlled trial. The effect of an exercise intervention on work-related fatigue will be compared to wait list. See Fig. 1 for an overview of the study design.

**Fig. 1 Fig1:**
[figure not shown]
Flow Diagram Study Protocol

### Ethical issues

The research plan has been approved by the Ethics Committee Faculty of Social Sciences of the Radboud University (registration number: ECSW2015-1901-278). Informed consent for participation in the study will be obtained from all participants.

### Participants and recruitment

Participants will be employees reporting high levels of work-related fatigue. Every employee – regardless job position – can sign up for participation. Participants will be recruited through advertisements with study information in personnel magazines, on facebook pages, and on intranet of large organizations in the region(s) in which the intervention will be carried out. Furthermore, advertisements and news items will be placed in (local) newspapers and on social media.

Inclusion criteria will be based on existing cut-off scores on two validated measures of work-related fatigue: a) ≥2.2 on the emotional exhaustion scale of the Dutch version of the Maslach Burnout Inventory [49]; b) ≥22 on the Fatigue Assessment Scale [50]. Participants can fill out these two scales on the study website (www.runtervention.nl). When participants score high on both scales, the researcher ([name]) will ask these participants for further information about exclusion criteria by email. Exclusion criteria will be: a) ≥ one hour exercising a week; b) fatigue attributable to a medical condition; c) currently or in the past six months receiving psychological and/or pharmacological treatment; d) drug dependence; e) contraindications to exercise. Contraindications to exercise will be measured by the Physical Activity Readiness Questionnaire (PAR-Q; [51]). Eligible participants will be invited for an appointment with the first author ([name]) or research assistants. During this appointment, the baseline measures (T0; except for the two measures of work-related fatigue that are already filled out) will be completed, the cognitive performance tests will be done, and the randomization procedure will be carried out. A separate appointment will be planned for the aerobic fitness test.

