### Randomization and blinding

Participants will be randomly assigned to either an exercise condition or a wait list condition at a 1:1 ratio. Because the intention is to conduct the exercise intervention in groups of 10 participants, randomization will be based on a block size of 20. When the number of 20 eligible participants in a block is reached, participants in the exercise intervention condition start the intervention and the participants in the wait list condition remain on the wait list. The randomization procedure will be carried out after the participant has completed the baseline measurement (T0). The randomization procedure will be executed by the first author ([name]) or research assistant, using sealed opaque envelopes. The participant opens the envelope and tells the researcher to which condition (s)he has been assigned.

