### Primary outcome measures

#### Work-related fatigue

We will use three self-reported indicators to measure work-related fatigue. First, *emotional exhaustion* will be assessed with the subscale ‘Emotional exhaustion’ of the Dutch adaptation of the Maslach Burnout Inventory [58], the Utrecht Burnout Scale (UBOS [59]). The scale consists of 5 items, for example “I feel burned out from my work” (0 = *never*, 6 = *every day*). A mean score equal to or higher than 2.2 on this scale is defined as a ‘high level’ of work-related fatigue [59]. Previous research shows that psychometric properties of this scale are good [60]. Secondly, *overall fatigue* will be measured with the 10-item Fatigue Assessment Scale (FAS [50]). An example question is “I get tired very quickly” (1 = *never*, 5 = *always*). A sum score higher than 21 is indicative of a high level of fatigue [61]. The scale has found to be valid and reliable [50]. Third, *need for recovery* will be assessed by a short version of the ‘Need for Recovery Scale’ [62]. The scale consists of 6 items. An example item is: “Because of my job, at the end of the working day I feel rather exhausted” (1 = *(almost) never*, 4 = *(almost) always*). For this scale, no norm scores are available. Therefore, inclusion was based on the measures UBOS and FAS. Previous research shows that validity is good [62].

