### Analyses of primary and secondary outcomes

We will use intention-to-treat analysis, meaning that all participants who are randomized to a condition will be included in the analyses. To test the efficacy of the exercise intervention (i.e. change in primary and secondary outcomes from pre [T0] to post [T6]), we will perform 2x2 repeated measures (M)ANOVAs with condition (exercise versus wait list) as between-subjects factor, and time (pre [T0] versus post [T6]) as within-subjects factor. We will conduct a RM-MANOVA for the three indicators of work-related fatigue together (*Hypothesis 1*). Furthermore, we will conduct separate RM-(M)ANOVAs for respectively self-efficacy (*Hypothesis 2a and 2b*), sleep (*Hypothesis 2c and 2d*), work ability (*Hypothesis 2e*), cognitive functioning (*Hypothesis 2f*), and aerobic fitness (*Hypothesis 2 g*). The Matching Task will be analyzed using a 2x2x2 mixed design ANOVA, with ‘run type’ (switch versus repetition), and time (pre versus post) as within-subjects factors, and condition as between-subjects factor (exercise versus wait list). In all analyses, we are particularly interested in the ‘condition x time’ interaction, because this indicates that the conditions differ from each other with respect to the development of the outcome measure over time. If applicable, significant interactions will be further examined by paired-sample t-tests. Partial eta-squared will be reported as effect size.

Additionally, to obtain more thorough insight into the clinical meaningfulness of the changes brought about by the exercise intervention [81], we will perform a Chi-Square Test to see if the number of participants who score below cut-off scores of fatigue after the intervention period (T6) differs between the intervention and the control condition (emotional exhaustion <2.2 on the UBOS; overall fatigue: <22 on the FAS).

To investigate whether intervention-effects last during the follow-up period, for each primary and secondary outcome measure, a repeated measures MANOVA will be performed to see whether it differs between pre (T0), post (T6), 6 weeks after the intervention period (T7), and 12 weeks after the intervention period (T8). If the overall time effect of MANOVA is significant, post hoc tests will be carried out to exactly determine between what time points the outcome had changed. As follow-up measures are only available for the intervention condition, the control condition will not be included in these analyses.

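### Website scores that decide entry are reused as T0 for two of three primary indicators, so regression to the mean enters the within-arm and exercise-only analyses

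*Protocol article*

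**What the plan says.** Under Participants and recruitment, entry requires "≥2.2 on the emotional exhaustion scale of the Dutch version of the Maslach Burnout Inventory" and "≥22 on the Fatigue Assessment Scale". "Participants can fill out these two scales on the study website"; for high scorers the researcher "will ask these participants for further information about exclusion criteria by email", and eligible people are then invited to an appointment. There, "the baseline measures (T0; except for the two measures of work-related fatigue that are already filled out) will be completed", and randomisation follows at the same visit.

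Under the primary outcome heading: "We will use three self-reported indicators to measure work-related fatigue". These are emotional exhaustion, overall fatigue and need for recovery. Table 1 lists all three at T0. Need for recovery has no norm score, so it was not an entry criterion.

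Under Analyses of primary and secondary outcomes: "We will conduct a RM-MANOVA for the three indicators of work-related fatigue together", with condition x time from T0 to T6 as the effect of interest. Significant interactions are followed by paired-sample t-tests. Persistence is tested over T0, T6, T7 and T8 in the exercise arm alone, because the wait-list arm has no T7 or T8.

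**The concern.** For exhaustion and FAS, one score is both the entry test and the pre-intervention value. A score that must exceed a threshold to be included is on average too high relative to the person's usual level, and the next measurement falls back with no treatment at all. Need for recovery is measured later and not selected on directly, so its T0 does not carry this artefact in the same way. The T0 of the primary outcome thus combines two occasions and two selection states.

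Where the arms are compared, the fall is common to both and cancels. Where one arm is examined alone, it does not cancel. It adds to the T0-T6 change in each paired t-test, and to every contrast of T0 with T6, T7 or T8 in the follow-up analysis. That analysis is the trial's only evidence that the effect lasts, and it has no control arm from which the artefact could be read off.

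**Working it through.** The documents give no figure for this point, so there is none to reproduce.

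**Inputs**
- From the protocol: selection on the website score, the same score used as T0, and 90 participants required, taken here as 45 per arm.
- Assumed: the share of applicants who pass the cut-off (50%, 70%, 85%) and the correlation r between any two measurements of a scale (.5, .7). Scores are standard normal among applicants, equally correlated over time, with no true change. Each scale is treated separately. SD means the SD among all applicants.

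**1. Expected fall with no treatment effect.** With cut-off c and pass rate p, the mean selected score is m = φ(c)/p, and the expected fall at the next measurement is (1 − r) × m.

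| p | c | m | fall, r = .5 | fall, r = .7 |
|---|---|---|---|---|
| 50% | 0 | .399/.50 = .798 | 0.40 | 0.24 |
| 70% | −0.524 | .348/.70 = .497 | 0.25 | 0.15 |
| 85% | −1.036 | .233/.85 = .274 | 0.14 | 0.08 |

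The range is 0.08 to 0.40 SD. If the scales are repeated at T0, the expected change from T0 to T6 is m × (correlation of sign-up with T6 − correlation of sign-up with T0). This is 0 when the two correlations are equal.

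**2. What the fall does to a within-arm test.** The variance of T6 minus the sign-up score among those included is (1 − r)² × V + 1 − r², where V = 1 − m(m − c) is the variance of the selected score.
- p = 50%, r = .5: V = .363, variance = .25 × .363 + .75 = .84. Expected paired t with 45 people: .40/√.84 × √45 = 2.9, so the artefact alone would usually pass 1.96.
- p = 85%, r = .7: V = 1 − .274 × 1.310 = .64, variance = .09 × .64 + .51 = .57. Expected paired t: .082/√.57 × √45 = 0.7, which is minor.

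**3. Arm comparison.** A simulation with no effect (45 per arm, cut-off at the mean, r = .7, t-test on change) rejected in 4.9% of runs. Both arms fell by 0.24 SD.

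**4. Precision if the scales are repeated.**
- Unadjusted change score, p = 50%: the variance goes from .84 to 2(1 − r) = 1.00 at r = .50. At r = .70 it goes from .09 × .363 + .51 = .54 to .60.
- If the sign-up T0 gave 80% power (1.96 + 0.84 = 2.80), a fresh T0 gives 2.80 × √(.84/1.00) = 2.57, about 73%, or 2.80 × √(.54/.60) = 2.66, about 76%.
- T6 adjusted for the sign-up score alone: 1 − r² = .75 or .51. Adjusted for sign-up and fresh T0: 1 − 2r²/(1 + r) = .67 or .42. These are reductions of 11% and 17%.
- T6 adjusted for the fresh T0 alone, p = 50%: .70 or .47.

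**The case against.** The strongest answer is that the primary test is sound. Selection happens before randomisation and is alike in both arms. A reader might infer that the reused score biases the treatment comparison; the design and the 4.9% error rate show that it does not. This part of the objection stands in full.

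It is also true that under the planned change-score test a repeated T0 costs precision, and that the 11% to 17% gain needs a different analysis. Much of that gain comes from having two baseline measurements rather than from the second being more recent. This stands, and it is why the repeat should not be adopted without the adjustment.

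Four further inferences are tempting and go too far.
- That fatigue at randomisation is never known: need for recovery and the weekly items, including fatigue and energy, are listed at T0. What is not known is standing against the two cut-offs.
- That the lack of a maximum interval from sign-up to appointment is a defect: an article may leave this to the full protocol. The model above gives time no role, so it says nothing about how stale the score is. The wait for the block, "When the number of 20 eligible participants in a block is reached, participants in the exercise intervention condition start the intervention", comes after T0 and would affect a repeated T0 as well.
- That many participants are below the cut-offs when randomised: with no true change, 8% to 33% would be below on one scale under the assumptions above. A wider set of assumptions gives 7% to 57% below on at least one of the two. No document figure narrows this.
- That repeating the scales cures dilution of the T6 cut-off comparison: the same people are randomised, so it does not.

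None of this answers the within-arm point. The reuse of the entry scores is stated outright, and the follow-up analysis has no control.

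**Conclusion.** The point holds for the within-arm paired t-tests and the exercise-only T0-T6-T7-T8 analysis of exhaustion and overall fatigue. There, a fall of about 0.08 to 0.40 SD is expected without any effect of exercise. At the upper end it would usually be significant by itself in an arm of 45; at the lower end it is small. The size depends on the assumed pass rate, the assumed retest correlation and a normal model for one scale at a time. The direction follows from the design whenever the retest correlation is below 1. The condition x time test of the primary outcome remains valid. This is a worthwhile and inexpensive improvement to the baseline, not a threat to the main comparison.

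**What to change.** - Repeat the UBOS exhaustion scale (5 items) and the FAS (10 items) at the T0 appointment, with need for recovery, before the envelope is opened. Use these scores as T0 in every analysis.
- Keep the website score for eligibility only and as a covariate.
- Analyse T6 adjusted for both the T0 score and the sign-up score, rather than as an unadjusted T0-T6 change.
- Report how many participants are still at or above both cut-offs at T0.

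Cost: fifteen items, a few minutes at a visit that already takes place, and a change to the primary model. Without the model change, the repeat costs precision, as shown in the working. Eligibility and the people randomised stay the same.

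Limits: the artefact is removed fully only if the sign-up score correlates equally with T0 and with later measurements. If it correlates more strongly with T0, part of the fall remains. The follow-up analysis also stays uncontrolled for the natural course of fatigue, and its report should say so.
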